**Experimental Procedure**

Participants who are screened positive (i.e., having a positive baseline biases) will be eligible to be recruited into the pilot randomized trial. Informed consent from these participants will have already been obtained in the screening stage. Participants who are ineligible (those without baseline biases) will be dismissed from the study, given due compensation and allowed to go on with their rehabilitation program. Members of the study team will orientate the participants on the use of the mobile application. Participants will be provided with a tablet device to use the mobile application daily. Participants will be also provided with a unique username and password to allow them to have access to the application daily. Participants will be required to complete the following baseline questionnaires, the baseline demographic and clinical information questionnaire, on Day 8 of their stay in the ward, or the first day of their intervention. The following baseline demographic and clinical information will be collected from the participants—that of nationality, gender, marital status, race, religion, highest level of education, housing conditions, current substance use, method of consumption of substance, quantity of substance consumed each time, frequency of use, previous treatment history, chronic diseases (psychiatric and physical disorders) and current psychiatric medications. Participants will also be required to complete a visual analogue scale for the assessment of cravings before and after undertaking the intervention. The experimental procedure will not differ for participants who are randomized to receiving the co-designed application versus that of the conventional application. Participants will be asked to spend 10 min to complete 200 repeats of the intervention task. Upon completion of the first intervention task, participants can rest for 10 min, before spending another 10 min to complete 200 repeats of the assessment task. Participants will continue to retake the intervention daily, each day they are an inpatient, except for weekends and public holidays. On the subsequent days, participants are to take the intervention task, rest for 10 min, before completing an assessment task. Participants will be asked to retake the craving questionnaire prior to and after the tasks on each of the days that they are involved in the study. Participants will be also asked to complete a questionnaire to acquire their feedback pertaining to the intervention (after they have completed three interventions). If participants request premature discharge from the ward, they are not required to return to the ward to complete the intervention. 

Participants will also be asked to complete a perspective/self-reported questionnaire on Day 3 of the intervention (i.e., when they have completed a total of three intervention tasks). This questionnaire has previously been used in our feasibility and acceptability study [15]. Participants will be asked the following questions:Prior to using the application, how confident were you in managing your addiction problem? (5-point Likert Scale)How easy was it to use the application? (5-point Likert Scale, ranging from Not at all to extremely, and written comments)How engaging was the application? (5-point Likert Scale, ranging from Not at all to extremely, and written comments)Do you feel motivated to continue to use the app? (5-point Likert Scale, ranging from Not at all to extremely, and written comments)Do the images in the app remind them of their substance use? (5-point Likert Scale)After using the app, how confident are you in managing your addiction problem? (5-point Likert Scale)

Figure 2 provides an overview of the study schedule/data collection time points and tasks participants are required to undertake. 

**c.** 

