### 2.3. Sampling and Recruitment

Convenience sampling will be used in the recruitment of participants over a period of 12 months, at the inpatient unit of the National Addictions Management Service (NAMS), Institute of Mental Health Singapore. The inpatient unit at NAMS offers a 2-week program, in which the first week of the program is focused on the provision of medication-assisted detoxification and the second week of the program is focused on rehabilitation. The unit can have a total of 22 inpatients at any one time. It is also crucial to note that the program is voluntary in nature, which implies that participants are free to leave the ward if they wish to, at any juncture of their inpatient treatment. All participants who have demonstrated interest in the study will be asked to undertake a baseline attention bias assessment task. Only participants who have baseline biases will be recruited into the trial and will be randomly assigned to any of the two groups by means of simple randomisation. Figure 1 provides an overview of the participant flowchart following screening and recruitment.

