### 2.4. Sample Size

For the purposes of this pilot, we plan to screen 60 participants for baseline biases. Based on our prior feasibility and acceptability study [15], approximately 50% of these participants will have baseline biases. We anticipate that 50% of the participants (or 30 participants) may not have baseline attentional biases and hence would not be eligible for the eventual pilot. Therefore, the sample size for the eventual pilot is that of 30 participants, with 15 participants being randomised to receiving the co-design application and the remaining 15 being randomised to receiving the conventional applications. The sample size of 30 participants in total, with 15 in each group, was selected, taking into consideration previous pilot randomized trials evaluating web-based cognitive bias interventions for individuals with obsessive-compulsive disorder [19,20]. In those previous studies, the sample size per group ranged from between 6 and 37 participants. Moreover, based on Bell LM et al. (2018)’s [21] guidance for using pilot studies in informing the design of confirmatory studies, the proposed sample size for the pilot study if the effect size is small (i.e., Cohen D is between 0.1 and 0.3), is an estimated 25 participants per arm of the intervention. We have not performed a power computation for the purposes of the pilot, as the pilot study is supposed to inform the definitive sample size for the confirmatory trial [22,23]. 

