**Screening for Eligibility**

Informed consent will be acquired from participants on the last day of their detoxification stay (Day 7), for the purposes of screening, in the presence of an impartial witness. For the screening for the presence of baseline attentional biases, participants are required to undertake an attention bias task on a tablet device. In the assessment task, participants will be shown a fixation cross for 500 milliseconds, followed by a set of images (one related to their substance of use and another neutral image that is similar in complexity). While 50% of these images will be presented for a short stimulus duration of 200 milliseconds, the other 50% of the set of images will be presented for a long stimulus duration of 2000 milliseconds. Following the disappearance of the images, participants are presented with a probe (in the form of an asterisk) for 200 milliseconds. Participants are required to indicate their response, by means of tapping the buttons on the screen, to indicate if the asterisk is presented on the left or right side. If they do not respond, they will be presented with the next trial. In the screening phase, 50% of the trials (100 trials) will involve the presentation of the probe with the substance image, and 50% of the remaining trials will involve the presentation of the probe with the neutral image. The presence of attentional bias will be computed by means of subtracting the reaction time that participants take to respond to probes that replace the neutral image from the reaction time to the probe that replaced the substance image. 

**b.** 

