### 4.1. Statistical Analyses

For data analysis, an intention to treat analytical approach will be used, to include all participants, including those who withdrew and those who are prematurely discharged from the inpatient unit. Microsoft Excel will be used for the computation of the attention bias scores for each participant for each of the assessment task, in accordance to this formula:(∑T_1_/n_1_) − (∑T_0_/n_0_),
where 

T_1_ refers to the time for probes that replaced the neutral stimulusn_1_ refers to number of trials for probes that replaced the neutral stimulusT_0_ refers to the time for probes that replaced the substance stimulusN_0_ refers to number of trials for probes that replaced the substance stimulus

SPSS Version 24.0 (SPSS Inc., Chicago, IL, USA) will be used for the analysis of the quantitative data. Demographic and clinical information data of the subjects in both groups will be summarized using descriptive statistics, including that of means and standard deviations. Chi-square tests will be used to determine if there are differences in the two groups for each of the demographic or clinical information variables. We plan to run ANOVA (analysis of variance) analysis to examine the differences in the outcome measure (attention bias scores/reaction time) across the time points in the actual definitive trial. P-values less than 5% will be considered statistically significant. 

For the qualitative data obtained by means of the perception questionnaire, the data will be coded using NVivo 12, and a thematic analysis approach will be used in the analysis. 

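### In the methods text the only pre-training bias score is the one used for selection, so a within-arm fall from screening is expected through regression to the mean even with no training effect

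*Protocol article*

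**What the plan says.** Screening takes place on Day 7: "Informed consent will be acquired from participants on the last day of their detoxification stay (Day 7), for the purposes of screening". Section 2.3 calls this screening task the baseline task: "All participants who have demonstrated interest in the study will be asked to undertake a baseline attention bias assessment task". Entry depends on its result: "Only participants who have baseline biases will be recruited into the trial", and the Experimental Procedure repeats the rule: "Participants who are screened positive (i.e., having a positive baseline biases) will be eligible to be recruited into the pilot randomized trial". No margin above zero and no repeat measurement is stated. Section 2.4 expects that "approximately 50% of these participants will have baseline biases".

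From Day 8 training comes first. On the first day: "Upon completion of the first intervention task, participants can rest for 10 min, before spending another 10 min to complete 200 repeats". Afterwards: "On the subsequent days, participants are to take the intervention task, rest for 10 min, before completing an assessment task". The baseline items listed for Day 8 are demographic and clinical questions. Craving is rated before and after the intervention, but bias is not.

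Both arms receive active training (section 2.1). Section 4.1 plans an ANOVA to "examine the differences in the outcome measure (attention bias scores/reaction time) across the time points"; the same sentence goes on to place that analysis in the definitive trial. The Abstract lists ANOVA among the analyses without that limit. Section 4 names recruitment within one year as the main outcome.

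**The concern.** A score that admits someone because it is above a cut carries, on average, favourable measurement error. On retest that error is not repeated, so the group mean moves back towards the population mean. The plan's own expectation of about 50% positive puts the cut at zero near the median of the score distribution, where measurement error decides eligibility for many people.

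The selected score is also the only one taken before training, and no untrained arm would show how much fall to expect without training. A fall from screening therefore cannot be separated from the selection artefact. This matters because the Introduction already cites a change among participants with baseline biases in the team's previous study as grounds for further work, and regression to the mean can imitate exactly that pattern. Section 4 acknowledges that only people with positive bias are selected, but treats it as a limit on generalisability, not as a source of apparent change.

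**Working it through.** **The plan's own figure.** Section 2.4: 60 screened × 0.50 positive = 30 randomised, 15 per arm. This reproduces. The previous study's opioid subgroup, as given in the Introduction, had 8 of 17 without bias, so 9/17 = 52.9% with bias, and 60 × 9/17 = 31.8. The two are consistent.

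**Model.** Screening and retest scores are taken as bivariate normal with equal SD, retest correlation r and no training effect; entry requires a screening score above zero. In units of the unselected SD, with p the share positive, z the normal quantile and φ the normal density:

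- population mean: μ = z(p)
- screening mean of those selected: μ + φ(μ)/p
- retest mean of those selected: μ + r·φ(μ)/p
- expected fall with no effect: (1 − r)·φ(μ)/p

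**Numbers at p = 0.5.** μ = 0 and φ(0)/0.5 = 0.399/0.5 = 0.80. The expected fall is (1 − r) × 0.80 SD.

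The documents give no r, so a range is assumed. The last two columns are simulated (20,000 trials per cell): a paired t-test of screening against one later score at two-sided 5%, counting only significant falls, for which the nominal rate is 5%/2 = 2.5%.

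| Assumed r | Expected fall (SD) | Share of screening mean | Significant fall, n = 30 | Significant fall, n = 15 |
|---|---|---|---|---|
| 0.2 | 0.64 | 80% | 87% | 56% |
| 0.4 | 0.48 | 60% | 73% | 42% |
| 0.6 | 0.32 | 40% | 53% | 28% |
| 0.8 | 0.16 | 20% | 28% | 15% |
| 0.9 | 0.08 | 10% | 16% | 10% |

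**Sensitivity at p = 9/17.** μ = 0.074 and φ(μ)/p = 0.75. The fall is 0.60, 0.30 and 0.15 SD at r = 0.2, 0.6 and 0.8, with significant falls at n = 30 in 83%, 48% and 25% of trials.

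**Between arms.** Under the same model, a two-sample t-test of change with 15 per arm rejected in 4.4% to 5.4% of trials across all values of r tried. Both arms are selected alike, so the artefact cancels in expectation.

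**Change between two scores that both come after selection.** The expected change is 0, and the simulated two-sided rejection rate at n = 30 was 4.9% to 5.0% for r from 0.4 to 0.8.

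**The case against.** The strongest reply is that this does not touch what the pilot is for. Its main outcome is recruitment, and section 4.1 assigns the ANOVA over time to the definitive trial, whose protocol is not shown. The scientific question set in the Introduction is whether the co-designed application does better than the conventional one, and that randomised contrast is not biased by selection. All of this stands. It limits the point to within-arm change from screening. It does not remove it, because the Abstract lists ANOVA without restriction and the pilot exists to test the procedures that the definitive trial will use.

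Second, a further pre-training assessment may exist. Figure 2 is not shown, and the Abstract says that enrolled participants complete a baseline assessment task. This cannot be excluded, but section 2.3 gives that name to the screening task, and the text schedules no other. Nor does section 4.1 say that screening will be the first time point; the artefact arises only if it is.

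Third, the size rests on an assumed r. That is so. A fall is expected for any r below 1, but it is small if the task is highly reliable.

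A reader might go further and infer that a reduction will be reported in both arms whatever the applications do, and that an inflated effect will then size the definitive trial. The documents do not support either step. With 15 per arm a significant fall is far from certain (10% to 56% over the range above). Section 2.4 says only that the pilot informs the later sample size, and no passage names within-arm change as the input. Nor should the fall be set beside the Cohen's d of 0.1 to 0.3 in section 2.4. That range is quoted for choosing the number per arm of a pilot, and nothing there makes it a change from screening.

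**Conclusion.** The point holds in a limited form. On the methods text, change from the Day 7 score within an arm cannot be read as a training effect: with no effect at all, the expected fall is (1 − r) × 0.80 SD when half screen positive. That is 0.64 SD at r = 0.2, 0.32 SD at r = 0.6 and 0.16 SD at r = 0.8. With all 30 participants pooled, a significant fall would appear in about 87%, 53% and 28% of trials.

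This assumes normal scores with equal SD, an r that the documents do not supply, screening used as the first time point, and no extra assessment in Figure 2. It also assumes that selection and analysis score bias in the same direction. As written they do not: the screening text subtracts the neutral-probe time from the substance-probe time, while the formula in section 4.1 does the reverse. If both were applied literally, the artefact would appear as a rise on the section 4.1 scale; it would not vanish.

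The recruitment outcome is unaffected, and the randomised comparison is not biased by this mechanism.

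**What to change.** **Wording, at no cost.** In section 4.1, state that evidence of effect is the between-arm difference in post-training bias score, adjusted for the screening score. Add that change from screening within an arm will not be interpreted as a training effect or used to size the definitive trial. Reconcile the Abstract with section 4.1 on whether the ANOVA belongs to the pilot.

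**Preferably also one added measurement.** Schedule a 200-trial assessment on Day 8 before the first intervention task, use it as the analysis baseline, and keep the screening score for eligibility only. It should have the screening format in both arms (half short and half long image durations, no feedback), because the co-designed arm's own assessment gives feedback and, under Table 1, starts at 10% short and 90% long. The cost is about 10 minutes per randomised participant, on the existing tablet. This removes the selection artefact but not other trends over time such as practice, so the between-arm difference should remain the basis for inference.

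**Score direction.** Define the bias score once, and use the same sign for screening and for section 4.1.

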**Details of Intervention Tools**

For the conventional mobile attention bias modification application, there are two tasks that participants are to undertake daily—that of the assessment task and that of the intervention task. In the assessment task, participants are presented with a fixation cross at the centre of the screen for 500 milliseconds. The fixation cross will then disappear, and a set of images will be presented. 50% of the set of images (i.e., 100 sets of images) will be presented for 200 milliseconds, and 50% of the set of the images (i.e., 100 sets of images) will be presented for 2000 milliseconds. The set of images will comprise a substance image and a neutral image, that is similar in colour, size and complexity. The images that will be used will be obtained from the Central Narcotics Bureau’s database. Following the disappearance of the images, a probe (asterisk) will appear, either replacing the substance image or the neutral image, for 200 milliseconds, before disappearing. Participants are supposed to indicate the position of the probe by selecting the buttons on the screen (i.e., left button if the probe is on the left side, right button if the probe is on the right side). In the assessment task, 50% of the time, the probe will replace the substance image, and in the remaining 50% of the time, it will replace the neutral image. Participants are to complete 200 repeats in the assessment task. There are 10 sets of images, which will be repeated 20 times over the 200 repeats. The time interval between each repeat is 250 milliseconds. In the intervention task, the procedure is like that of the assessment task, with the exception that the probe will always replace the neutral image (100% of the time). This allows for the retraining of biases away from the substance image, and towards that of the neutral image. Participants are to also complete 200 repeats during the intervention task. 

For the co-designed intervention, there are also two tasks that participants are to undertake daily, that of the assessment and that of the intervention task. The application contains an instructional video to help participants better understand what they would need to do in these tasks. Participants are to complete 5 sample trials before they undertake the assessment or intervention task. In the assessment task, participants are presented with a fixation cross at the centre of the screen for 500 milliseconds. The fixation cross will then disappear, and a set of images will be presented. The duration for which the images stay on the screen will vary across the days of the intervention. Table 1 provides an overview of the timings of the images by days of the intervention. 

The set of images will comprise of a substance image and a neutral image which is similar in colour, size and complexity. The images that are used will be obtained from the Central Narcotics Bureau’s database. Following the disappearance of the images, a probe (asterisk) will appear, either replacing the substance image or the neutral image for 200 milliseconds, before disappearing. Participants are supposed to indicate the position of the probe by selecting the buttons on the screen (i.e., left button if the probe is on the left side, right button if the probe is on the right side). If participants responded correctly, they will be presented with a smiley emoji. If they have not responded correctly, they will be presented with a frowning emoji. The scores that they have accumulated across the trials will be presented on the top right-hand corner of the application. Participants are to complete 200 repeats in the assessment task. There are 10 sets of images, which will be repeated 20 times over the 200 repeats. Participants will be presented with their final scores upon the completion of the task. The time interval between each repeat is 250 milliseconds.

In the intervention task, the procedure is like that of the assessment task, but with the exception that the probe will now always replace the neutral image, to allow for retraining of biases away from the substance stimulus. 

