**Figure 2 ijerph-17-00752-f002:**
[figure not shown]
Overview of the data collection time points and tasks to be undertaken.

**Table 1 ijerph-17-00752-t001:** Overview of timings of the images by the days of intervention.

Day of Intervention	Total Number of Trials	Percentage of Image Sets Presenting for 200 Milliseconds	Percentage of Image Sets Presenting for 2000 Milliseconds
Day 1	200	10%	90%
Day 2	200	20%	80%
Day 3	200	30%	70%
Day 4	200	40%	60%
Day 5	200	50%	50%

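### The co-designed arm's daily assessment task differs from the conventional one and changes from Day 1 to Day 5, so its bias scores partly reflect the instrument

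*Protocol article*

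**What the plan says.** Section 3.c (Details of Intervention Tools) fixes the conventional assessment at 200 repeats: "50% of the set of images (i.e., 100 sets of images) will be presented for 200 milliseconds". The other half stays on screen for 2000 ms. The screening task in section 3.a has the same even split. No feedback, score display or practice trials are described for either.

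For the co-designed application, the timing sentence stands inside the description of the assessment task: "The duration for which the images stay on the screen will vary across the days of the intervention". It refers to Table 1, which runs from 10% short and 90% long images on Day 1 to 50% of each on Day 5. The same description adds feedback ("If participants responded correctly, they will be presented with a smiley emoji", with a frowning emoji for errors) and a score display: "The scores that they have accumulated across the trials will be presented on the top right-hand corner of the application". Practice is also added: "Participants are to complete 5 sample trials before they undertake the assessment or intervention task". The co-designed intervention task is then defined as like this assessment task except that the probe always replaces the neutral image. The timings and feedback therefore apply to both tasks.

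Section 3.b states: "The experimental procedure will not differ for participants who are randomized to receiving the co-designed application versus that of the conventional application".

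Section 4.1 computes one bias score per assessment task: mean time to probes replacing neutral images minus mean time to probes replacing substance images. The formula has no term for image duration. An ANOVA of bias scores or reaction time across time points is planned for the definitive trial.

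**The concern.** The Introduction says the co-designed application needs evaluating against the original to see whether it is more effective. The bias score is the natural measure for that. If the task producing the score differs by arm, and in one arm also by day, the two arms can score differently, and the co-designed arm can drift, when training has done nothing.

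The direction of the artefact is unknown. If bias is larger at 2000 ms than at 200 ms, the co-designed arm starts too high and falls day by day, which looks like progress. If bias is larger at 200 ms, that arm starts too low and rises, which looks like an early benefit that is then lost. A pilot that rehearses the definitive trial would hand this problem on to it.

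**Working it through.** **The plan's own figure.** Conventional assessment: 10 image sets × 20 = 200 repeats, and 200 × 50% = 100 at each duration. This agrees with section 3.c.

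**Inputs.** Let p be the share of 200 ms trials. Conventional arm and screening: p = 0.5 (sections 3.c and 3.a). Co-designed arm: p = 0.1, 0.2, 0.3, 0.4, 0.5 on Days 1 to 5 (Table 1). Let b200 and b2000 be a participant's bias at each duration, in the sense of section 4.1. The documents give neither value.

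**Formula.** Assume that durations are balanced over probe positions. The pooled score is then

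score = p × b200 + (1 − p) × b2000.

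With no training effect, co-designed minus conventional is

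[p × b200 + (1 − p) × b2000] − [0.5 × b200 + 0.5 × b2000] = (0.5 − p) × (b2000 − b200).

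**Result by day**, for assumed gaps b2000 − b200 of 5, 10, 20 and 40 ms (negative gaps reverse the sign):

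| Day | 200 / 2000 ms trials, co-designed | Conventional | Multiplier of gap | 5 ms | 10 ms | 20 ms | 40 ms |
|---|---|---|---|---|---|---|---|
| 1 | 20 / 180 | 100 / 100 | 0.4 | 2 | 4 | 8 | 16 |
| 2 | 40 / 160 | 100 / 100 | 0.3 | 1.5 | 3 | 6 | 12 |
| 3 | 60 / 140 | 100 / 100 | 0.2 | 1 | 2 | 4 | 8 |
| 4 | 80 / 120 | 100 / 100 | 0.1 | 0.5 | 1 | 2 | 4 |
| 5 | 100 / 100 | 100 / 100 | 0 | 0 | 0 | 0 | 0 |

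The matching Day 1 to Day 5 drift within the co-designed arm is (0.5 − 0.1) × (b200 − b2000), that is, 0.4 times the gap with the sign reversed. The conventional arm has no such drift, because its p never changes.

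**With a common 50/50 assessment**, p = 0.5 in both arms on every day and the multiplier is 0 throughout.

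**Fallback scoring.** Averaging the two duration-specific scores with equal weight removes p from the expected score. The cost is precision. On Day 1 the co-designed arm has 10 short and 90 long trials per probe position, against 50 and 50 in an even task. With equal trial variance and an even probe split, the variance ratio is (1/10 + 1/90) / (1/50 + 1/50) = 0.1111 / 0.04 = 2.78.

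**How secure Day 5 is.** Sessions start on Day 8 of a two-week programme and skip weekends and public holidays (sections 2.3 and 3.b). Days 8 to 14 are seven consecutive days and contain five weekdays, so at most five sessions fit. One public holiday, or a voluntary early discharge, removes the fifth.

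**The case against.** The strongest reply is that this is a pilot whose main outcome is recruitment within a year, together with whether randomisation and administration work (section 4). None of these uses the bias score, and section 4.1 places the ANOVA in the definitive trial, although the Abstract lists ANOVA without that limit. This stands. It limits the harm to the score and to the design being rehearsed. It does not remove the harm, because the Introduction gives finding such problems as the pilot's purpose.

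A reader might infer that no arm difference and no trend could be attributed to training. The documents do not support that. The duration mix is equal on Day 5 and at screening, so the Day 5 arm contrast and the screening-to-Day 5 change are free of the duration part. The conventional arm's trend has no duration drift at all.

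A reader might also see a flat contradiction with section 3.b. That sentence names the two applications and leads into the session routine, so it can fairly be read as covering order and workload only. It needs clarifying, not more.

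On feedback, no figure in the documents shows an effect. An equal additive change in speed on all trials cancels in the bias score, though not in raw reaction time, which section 4.1 also names. Whatever remains is of unknown size and direction.

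Finally, Table 1 may have been meant for training only. If so, the wording needs correcting, because the sentence stands in the assessment task. The duration part could be repaired in analysis if stored trials are labelled by duration; the feedback difference could not.

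**Conclusion.** The point holds and should be fixed. As written, the co-designed assessment differs from the conventional and screening assessments in duration mix on Days 1 to 4, and in feedback, score display and sample trials on all days.

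Given balance of durations over probe positions, the duration mix alone creates an arm difference of 0.4, 0.3, 0.2, 0.1 and 0 times (b2000 − b200) on Days 1 to 5, with a matching drift in the co-designed arm. The gap is not in the documents. Assumed gaps of 5 to 40 ms give 2 to 16 ms on Day 1, and the artefact is zero if bias is the same at both durations. The Day 5 comparison escapes this part but still carries the feedback difference, and Day 5 is the session most easily lost.

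What is affected is the bias score and the definitive design. The pilot's recruitment outcome is untouched.

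**What to change.** Use one assessment task in both arms on all days: the screening and conventional version, with half the images at 200 ms and half at 2000 ms, and no emoji or score. Confine the Table 1 timings and the feedback to the co-designed intervention task. The contrast in training is kept. The cost is a change to the application and to the wording of section 3.c, and co-designed participants would see two task formats per session. The documents do not show how easily the application allows this separation.

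If the application cannot be changed, score the 200 ms and 2000 ms trials separately and average them with equal weight in both arms. This requires trial records labelled by duration. It costs precision early on (Day 1 variance in the co-designed arm is about 2.8 times that of a 50/50 task), and the report must say that the feedback difference remains.

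In either case, state in section 3.b that the sameness of procedure refers to the session schedule only.
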